### Criteria for discontinuing or modifying allocated interventions {11b}

Subjects can leave the study at any time for any reason if they wish to do so without any consequences. The investigator can decide to withdraw a subject from the study intervention for urgent medical reasons.

### Strategies to improve adherence to interventions {11c}

Patient will be reminded by the local research staff to start with study medication 3 days prior to the operation date. A daily check by research staff will take place for compliance but only during admission; in the three preoperative days no check will be performed apart from the reminder prior to the start, as not to interfere with the pragmatic nature of the trial.

### Relevant concomitant care permitted or prohibited during the trial {11d}

All medication considered necessary for the patient’s welfare will be continued. Relevant concomitant medication, such as anticoagulants and corticosteroids, will be recorded within the eCRF. The use of sucralfate is prohibited as it is able to bind to components of the SDD and therefore reduces its effectiveness. If necessary, sucralfate can be substituted with an agent that has a different mechanism of action.

### Provisions for post-trial care {30}

The sponsor/investigator has a liability insurance that is in accordance with article 7 of the WMO (Dutch: “Wet Medisch-Wetenschappelijk Onderzoek met Mensen”; English: Act/law on Medical Research Involving Human Subjects). The sponsor has an insurance that is in accordance with the legal requirements in The Netherlands (article 7 WMO). This insurance provides cover for damage to research subjects through injury or death caused by the study. The insurance applies to the damage that becomes apparent during the study or within 4 years after the end of the study. For the Belgian centers, the insurance provided by the Belgian Coordinating Center will be covering no-fault liability for Belgian participants.

### Outcomes {12}

#### Primary outcome

The primary outcome parameter is the cumulative incidence of postoperative pneumonia within 30 days after surgery. Pneumonia will be defined by the following criteria: positive sputum culture or the presence of a new progressive radiographic infiltrate plus at least two of the following clinical features: fever > 38.5 °C, leucocytosis (> 11.0*10^9/L) or leukopenia (< 4.0*10^9/L), or purulent secretions.

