## Abstract

**Background:**

Esophagectomy is a highly complex surgical procedure, and it is associated with significant morbidity and mortality. The postoperative complication rate is high, with pneumonia being the most common. These are thought to arise from (micro-)aspiration of bacteria residing in the oropharyngeal and gastrointestinal (GI) tract. Selective decontamination of the digestive tract (SDD) is a prophylactic antibiotic strategy aimed at preventing these infections. SDD decolonizes the oropharyngeal and GI tract from pathogenic aerobic gram-negative rods, fungi and yeasts, while anaerobic, protective microbiota are preserved. The PERSuaDER trial aims to evaluate whether perioperative SDD can reduce postoperative pneumonia after esophagectomy.

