## Introduction

### Background and rationale {6a}

The incidence of esophageal carcinoma has increased considerably within the last thirty years worldwide and is expected to keep on rising [1, 2]. This change will likely lead to an increase in the number of esophagectomies that will be performed. Despite the implementation of minimally invasive surgical techniques, these surgeries are regularly accompanied by infectious complications, with postoperative pneumonia being among the most common (up to 40%) and anastomotic leakage (10–20%) the most dreaded [3–6]. These complications lead to an increase in hospitalization time, healthcare costs, and decreased long-term survival [7–9].

Postoperative pneumoniae are thought to arise from (micro-)aspiration of bacteria residing in the oropharyngeal and gastrointestinal (GI) tract [10]. Besides causing respiratory infections, these pathogens might also be able to induce local inflammation and abscess formation at the level of the esophago-enteric anastomosis, resulting in anastomotic dehiscence and eventually anastomotic leakage [11]. Therefore, it is hypothesized that eliminating these pathogens prior to surgery and during recovery potentially decreases the risk of postoperative infections and subsequent anastomotic leakage.

Aiming to prevent postoperative complications, some hospitals in the Netherlands already use a perioperative prophylactic antibiotic strategy that reduces GI colonization with aerobic gram-negative rods and yeasts, while preserving anaerobic microbiota [12]. This strategy, named selective decontamination of the digestive tract (SDD), consists of three oral, non-absorbable antimicrobial agents (colistin, tobramycin, and amphotericin B) that are administered four times daily as an enteral suspension [13]. SDD is associated with a reduced risk of ventilator-associated pneumonia in intensive care unit (ICU) patients [14].

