#### Microbial assessment

Two microbial samples will be taken from the esophageal resection specimen (one from the proximal and one from the distal part) for culture in the control as well as in the intervention group to evaluate the effectiveness and compliance of SDD application.

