## Assignment of interventions: blinding

### Who will be blinded {17a}

As an open label study, allocation of the intervention will not be blinded. Analysis of the outcome parameters will be blinded.

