## Discussion

Esophagectomies are often followed by (infectious) complications, especially pneumonia. To reduce the risk of pneumonia, some hospitals in the Netherlands already use SDD. However, the scientific evidence remains limited. The large studies demonstrating the safety and efficacy of SDD in reducing infectious complications and mortality were never conducted in esophageal patients. These trials primarily involved patients in intensive care units or those undergoing elective (mostly lower) gastrointestinal surgery [14, 29, 30]. To date, little evidence exists regarding the perioperative use of SDD in esophageal cancer surgery. The few studies addressing this population are generally observational, vary in SDD composition and duration and are often small or of lower quality.

We designed a large, open-label randomized controlled trial comparing standard care with SDD to standard care without SDD, to find the much-needed evidence on the efficacy of SDD in patients undergoing esophageal cancer surgery. We selected the most widely used SDD formulation, combining amphotericin-B, colistin and tobramycin to target not only the most common bacterial pathogens, namely gram-negative rods, but also yeasts. Our study does have some limitations. A key point to consider is that no placebo will be used in our trial. Patients receiving SDD in addition to standard care will be compared to a control group receiving standard care without a placebo. Incorporating a placebo in this large, investigator-initiated drug trial was deemed impractical, as a significant portion of the intervention occurs at home without study staff supervision. This design reflects a real-life scenario, in contrast to the potential selection bias that may arise in placebo-controlled trials. However, the absence of a placebo increases the risk of biased outcome assessment. To mitigate this, we have implemented objective criteria for the primary endpoint. Furthermore, global shortages of SDD components may require adjustments to the composition of our investigational medicinal product (IMP). However, a suitable alternative is available, and such modifications also occur in clinical practice. Therefore, the intervention remains well-defined and reflective of real-world conditions, making the intervention sufficiently well-defined.

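### The primary pneumonia definition has two readings, neither requires an infiltrate, and its sputum-culture criterion can be changed by SDD itself

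*Protocol article*

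**What the plan says.** Under Primary outcome, the article states: "The primary outcome parameter is the cumulative incidence of postoperative pneumonia within 30 days after surgery". The qualifying rule is "positive sputum culture or the presence of a new progressive radiographic infiltrate plus at least two of the following clinical features". The features listed are a temperature above 38.5 °C, "leucocytosis (> 11.0*10^9/L) or leukopenia (< 4.0*10^9/L), or purulent secretions". No other section says how the conjunctions group.

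On what SDD does, the Abstract states: "SDD decolonizes the oropharyngeal and GI tract from pathogenic aerobic gram-negative rods, fungi and yeasts". Background and rationale {6a} names the same flora as the source of the disease: "Postoperative pneumoniae are thought to arise from (micro-)aspiration of bacteria residing in the oropharyngeal and gastrointestinal (GI) tract". Under Microbial assessment, swabs of the resection specimen are taken "for culture in the control as well as in the intervention group to evaluate the effectiveness and compliance of SDD application".

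On blinding, section {17a} says: "As an open label study, allocation of the intervention will not be blinded", although the outcome analysis is to be blinded. Section {5d} describes the three adjudicators of the primary endpoint as not blinded. Section {18a} takes primary endpoint data from medical records. The Discussion accepts that having no placebo raises the risk of biased outcome assessment and answers that "we have implemented objective criteria for the primary endpoint".

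**The concern.** There are two linked problems.

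1. **Ambiguity.** Reading A is culture alone, or (infiltrate plus at least two features). Reading B is (culture or infiltrate), plus at least two features. A patient with a positive sputum culture and fewer than two features is an event under A and not under B. This is the only primary endpoint, and the trial is recruiting.

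2. **A criterion that the treatment can change.** Under both readings a positive culture can stand in for the infiltrate. Sputum is expectorated through the oropharynx that SDD is meant to decolonise. A control patient may therefore qualify by culture where the same patient under SDD would not, with no difference in lung disease. Objective criteria protect against a biased assessor. They do not protect against a test result that the drug itself alters, and blinding the adjudicators would not repair that either. Because allocation is open, staff who decide whether to send sputum may also know the arm.

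At stake is whether a lower event rate under SDD can be read as prevention of pneumonia, which is the stated focus of the primary objective.

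**Working it through.** **Inputs from the article (Sample size {14}).** Control rate 22%, SDD rate 13%, 90% power, two-sided alpha 0.05, looks at 30% and 60%, 407 per arm before dropout.

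**The plan's own figure.** The pooled-variance formula for 22% vs 13% gives 373 per arm for a fixed design. The Hwang-Shih-DeCani parameters are not stated. With assumed parameters (efficacy −4, futility −2) the group-sequential inflation factor is 1.0615, and 373 × 1.0615 gives 396. With (−2, −2) it is 1.0871, and 373 × 1.0871 gives 406. The stated 407 is reproduced within 3%.

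**Assumptions not in the article.** Let b be the infiltrate-confirmed rate, equal in both arms (no effect of SDD). Let c be the share of the remaining controls who qualify only through culture. SDD is assumed to halve c.

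- Control: p1 = b + (1 − b)c
- SDD: p2 = b + (1 − b)c/2
- Chance of a significant result for SDD: Φ[(p1 − p2 − 1.96·SE0)/SE1]
- SE0 = √[2p̄(1 − p̄)/407], where p̄ is the mean of p1 and p2
- SE1 = √{[p1(1 − p1) + p2(1 − p2)]/407}

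The pairs (b, c) were chosen so that p1 stays at about 22%.

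| b | c | p1 | p2 | p2/p1 | Culture-only share of control events | Chance of significance |
|---|---|---|---|---|---|---|
| 20% | 2.5% | 22.0% | 21.0% | 0.95 | 9% | 5.3% |
| 18% | 5% | 22.1% | 20.05% | 0.91 | 19% | 10.7% |
| 15% | 8% | 21.8% | 18.4% | 0.84 | 31% | 22.7% |

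Middle row written out: p1 = 0.18 + 0.82 × 0.05 = 0.2210; p2 = 0.18 + 0.82 × 0.025 = 0.2005; SE0 = 0.02859; SE1 = 0.02858; (0.0205 − 0.0560)/0.0286 = −1.24; Φ = 0.107. The nominal one-sided error is 2.5%.

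**How much would have to be lost.** With 90 control events in 407 (22%), nominal significance first appears at 67 SDD events (16.5%, z = 2.04). That is a loss of 23/90, about 26% of events.

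**Power if an infiltrate were mandatory.** With b = 18% and a 40% reduction, the rates are 18% vs 10.8%, and (0.072 − 1.96 × 0.02461)/0.02448 = 0.97, so power is about 83% at 407 per arm. The same fixed-design formula gives 92% for 22% vs 13%.

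**The case against.** The case for the present definition has real weight.

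- **Reading B asks for signs of infection.** A culture-positive patient who also has two of fever, abnormal leucocytes and purulent secretions is not merely colonised. The article does not say that only infiltrate-confirmed disease is pneumonia. This stands, and it makes the problem smaller on reading B. It does not remove it, because the culture result still decides whether such a patient without an infiltrate counts.
- **Fewer pathogens is the proposed mechanism of benefit.** A fall in culture-positive, symptomatic cases may be genuine prevention. This also stands. The difficulty is that the endpoint cannot separate the two explanations.
- **The suppression is limited.** The article names gram-negative rods, fungi and yeasts, not every organism that sputum may grow. Dosing ends on day 3 (Table 1), while the endpoint runs to day 30. Halving culture-only events over the whole window is therefore an assumption and may be too strong.
- **The calculation is simplified.** The planned analysis is stratified Cox regression with interim looks; the figures above are for a fixed two-proportion test.

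A reader might go further and infer that the trial could reach its planned result without preventing any pneumonia, or that the false-positive chance is 20% to 49%. The documents do not support either as an expectation. With 18% infiltrate-confirmed, chances of 20%, 28% and 49% come from culture-only rates of 8% vs 4%, 10% vs 5% and 10% vs 3%. These imply control rates of 24.6%, 26.2% and 26.2%, above the planned 22%. Moving from 22% to 13% by culture suppression alone would need about 41% of control events to disappear (1 − 13/22).

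**Conclusion.** The concern holds in a limited form. The ambiguity is certain: the text supports two readings that count different patients, neither requires an infiltrate, and nothing elsewhere in the article settles it. That culture is not neutral to treatment follows from the article's own account of SDD. The direction of bias is towards SDD, largest if culture alone qualifies.

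The size is not known. At about the planned control rate, the illustration gives a false-positive chance of roughly 5% to 23% instead of 2.5%, and an apparent risk ratio of 0.95 to 0.84. It rests on assumed culture-only shares of 9% to 31% of control events, on SDD halving them, and on those losses being artefact. A result produced wholly by culture suppression is an extreme case. Smaller shares still shift the estimate and leave the meaning of a positive result open.

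**What to change.** 1. Rewrite the definition with explicit brackets so that a positive culture without at least two of the listed clinical features cannot qualify.
2. Have the adjudicators record, for every event, the route by which it qualified: infiltrate, culture or both, and which features were present.
3. Pre-specify a key sensitivity analysis of the primary outcome that counts only events with a new or progressive infiltrate plus at least two features.

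**Cost.** A wording change, submitted as a modification if it counts as substantial; a field on the adjudication form; and re-coding of any cases already adjudicated. The event count falls slightly if culture-alone cases have been counted, and the restricted analysis is less precise.

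Making an infiltrate mandatory for the primary endpoint itself is an option only if the control rate and power are restated. At 18% vs 10.8% and 407 per arm, fixed-design power is about 83%, and the change would be made in an open-label trial that is already recruiting.

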#### Secondary outcomes

Secondary endpoints include the incidence of postoperative complications, such as anastomotic leakage based on Esophageal Complications Consensus Group (ECCG) criteria, and the rate of reoperation within 30 days following surgery [21]. Complications will be graded according to the modified Clavien-Dindo classification [22]. Other secondary endpoints are postoperative length of stay in the hospital and the intensive care unit (ICU), as well as readmissions within 6 months after surgery, mortality, quality of life (QoL), direct and indirect costs, medication adherence, and side effects.

#### Microbial assessment

Two microbial samples will be taken from the esophageal resection specimen (one from the proximal and one from the distal part) for culture in the control as well as in the intervention group to evaluate the effectiveness and compliance of SDD application.

#### Questionnaires and diaries

Patients in both the intervention and control arms will be asked to keep a diary during the perioperative period. This allows us to explore potential side effects, therapy adherence and real-life experiences of patients. Quality of Life (QoL) will be measured by three validated questionnaires (EORTC OG25, QLQC30 and EuroQol-5D-5L) provided to patients 1 week before surgery, and at 30 days, 3 months, and 6 months postoperatively [23, 24]. We will estimate direct and indirect health-related costs with the help of a medical consumption and productivity cost questionnaire developed by the iMTA [25, 26]. These questionnaires will be provided to the participants together with the QoL questionnaires at 3 and 6 months postoperatively.

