### Objectives {7}

The primary objective of the PERSuaDER trial is to evaluate the effect of SDD on infectious complications after esophagectomy, focusing on the prevention of pneumonia. Based on the afore mentioned findings, the hypothesis is that SDD will decrease the rate of post-operative pneumonia by 40% [15]. Secondary objectives are to determine additional benefits such as reduction of other infectious complications including anastomotic leakage, quality of life during the recovery period and evaluation of the risks of SDD. To support broader implementation, patient diaries will be used to collect data on patient preference and adherence, which are critical factors for the broader implementation of SDD. Additionally, a cost-effectiveness analysis will be conducted.

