#### Participant timeline {13}

Participant timeline is outlined in Table 1.

**Table 1 Tab1:** Schedule of assessments and study procedures

	Study period										
	**1–6 weeks until surgery**	**D-3**	**D-2**	**D-1**	**D0**	**D1**	**D2**	**D3**	**D30**	**D90**	**D180**
	Outpatient clinic	Home		Hospital					Home		
Screening study eligibility	x										
Advising pregnancy test if applicable	x										
Information on PERSuaDER, study content and consent	x										
Collection informed consent	x										
Randomization	x										
Dispersion and instruction on intervention medication	x										
SDD intervention		x	x	x	x	x	x	x			
Patient diary		x	x	x	x	x	x	x			
Resectional specimen swabs					x						
Pneumonia assessment									x	x	x
Other complications assessment*									x	x	x
Medication adherence assessment									x		
QoL questionnaires	x								x	x	x
Other secondary outcome assessment*									x	x	x
(S)AE, SUSAR assessment **		x	x	x	x	x	x	x	x	x	x

* Other secondary outcomes: postoperative length of stay, the intensive care unit (ICU) length of stay, re-admissions, cost assessment. ** As described in the “Adverse event reporting and harms {22}” section*. QoL*, Quality of Life; *(S)AE*, (Serious) Adverse Event; *SUSAR*, Suspected Unexpected Serious Adverse Event

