### Data collection and management

#### Plans for assessment and collection of outcomes {18a}

During the outpatient visit at which inclusion takes place, the patient will be assigned an anonymized participation number. The key needed to identify the patient data is held by the Principal Investigator (PI) of the participating sites. During the trial, data will be collected by delegated research personnel, who are listed in the delegation log. Data for the primary, and most secondary endpoints will be collected from the patient’s medical records. Data on secondary endpoints regarding quality of life and other patient-derived outcome measures (i.e., patient diary) will be collected through questionnaires (paper-based or through CastorEDC). Data on IMP accountability will be gathered from patient medical records, patient diary, and a dedicated IMP-accountability form. This data will be entered into the electronic case report forms (eCRF). Data such as source documents will be maintained at the participating site for 25 years after the end of this study, conforming to European Union Clinical Trials Regulation (EU-CTR).

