### Methods in analysis to handle protocol non-adherence and any statistical methods to handle missing data {20c}

The amount of missing data will be described. Missing data in variables that are planned to be included in multivariable models will be imputed using multiple imputation. Missing outcome variables and missing data in planned subgroup variables will not be imputed.

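### The ban on imputing missing outcomes makes no exception for questionnaire-based costs and EQ-5D-5L utilities, so that part of the cost-effectiveness analysis rests on responders

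*Protocol article*

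**What the plan says.** The Objectives section {7} states: "Additionally, a cost-effectiveness analysis will be conducted". The Secondary outcomes section lists "mortality, quality of life (QoL), direct and indirect costs, medication adherence, and side effects", alongside hospital and ICU stay, readmissions to 6 months and reoperation.

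For costs, Questionnaires and diaries says: "We will estimate direct and indirect health-related costs with the help of a medical consumption and productivity cost questionnaire developed by the iMTA". On timing: "These questionnaires will be provided to the participants together with the QoL questionnaires at 3 and 6 months postoperatively". The quality-of-life instruments, including EQ-5D-5L, are "provided to patients 1 week before surgery, and at 30 days, 3 months, and 6 months postoperatively".

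On sources, section {18a} says "Data for the primary, and most secondary endpoints will be collected from the patient" (the sentence goes on to name the medical records). Quality of life and other patient-derived measures come from questionnaires.

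On missing data, section {20c} plans multiple imputation for variables entering multivariable models and then adds: "Missing outcome variables and missing data in planned subgroup variables will not be imputed". No outcome is exempted.

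**The concern.** Costs and EQ-5D-5L values are outcomes, so the rule in {20c} covers them. Inpatient care can be read from the hospital record. Care outside hospital, lost productivity and utility can be known only if the patient replies. Where a reply is missing, the plan as written leaves the item missing.

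This matters because the missingness is unlikely to be random. A patient recovering from pneumonia, a leak or a reoperation is plausibly less likely to return a form, and these are events that SDD is intended to prevent. If the control arm has more of them, it may lose more of its costly, low-utility patients. The questionnaire-based comparison would then describe responders and not the randomised groups, although section {18b} promises intention-to-treat analysis for participants who drop out during follow-up.

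**Working it through.** **1. Which items the rule reaches.** The article does not divide costs between sources. Setting its sections side by side gives:

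| Item | Needs patient reply? | When |
|---|---|---|
| Hospital stay, ICU stay, reoperation, readmissions | No, if taken from records ({18a}) | To 30 days or 6 months |
| Care outside hospital, productivity | Yes | Forms at 3 and 6 months |
| EQ-5D-5L utility | Yes | Before surgery, 30 days, 3 and 6 months |
| Costs and utility after death | No, zero by definition | After death |

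The ban on imputation bites on the second and third rows only.

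**2. Is there a figure in the plan to reproduce?** No. The article gives no response rate, mortality or unit cost, so the bias cannot be calculated from it. What follows is an illustration.

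**3. Illustration.** Inputs from Sample size {14}: pneumonia 22% in controls and 13% with SDD, a true contrast of 22 − 13 = 9.0 points. Assumptions:
- pneumonia is the only driver of the cost difference;
- response is b = 90% without pneumonia and a with pneumonia;
- a and b are the same in both arms.

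Pneumonia share among responders = p·a / (p·a + (1 − p)·b).

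For a = 70%:
- control: 0.22 × 0.7 / (0.22 × 0.7 + 0.78 × 0.9) = 0.154 / 0.856 = 0.1799
- SDD: 0.13 × 0.7 / (0.13 × 0.7 + 0.87 × 0.9) = 0.091 / 0.874 = 0.1041
- difference 0.0758; understatement 1 − 0.0758/0.09 = 15.8%

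| a | Control | SDD | Difference | Understated by |
|---|---|---|---|---|
| 90% | 0.2200 | 0.1300 | 0.0900 | 0% |
| 80% | 0.2005 | 0.1172 | 0.0832 | 7.5% |
| 70% | 0.1799 | 0.1041 | 0.0758 | 15.8% |
| 60% | 0.1583 | 0.0906 | 0.0677 | 24.8% |
| 50% | 0.1355 | 0.0767 | 0.0588 | 34.6% |

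**4. Scaling to the whole cost difference.** If a share s of the pneumonia-related cost is seen only through questionnaires and the rest is taken from records for everyone, the total is understated by s times the last column. The article does not give s. At s = 0 there is no understatement; at s = 1 the table applies in full.

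**5. Is the direction fixed?** Only if response depends on pneumonia equally in both arms, which an open-label trial does not guarantee. Mixing rows of the table shows this:
- a = 70% in controls and 80% with SDD: 0.1799 − 0.1172 = 0.0627, understated by 30%
- a = 80% in controls and 70% with SDD: 0.2005 − 0.1041 = 0.0964, overstated by 7%

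**The case against.** **Questionnaires are not said to be the only cost source.** A reader might infer that all costs rest on the forms and that patients who die or do not reply leave the cost comparison altogether. The documents do not support this. The wording is that costs are estimated with the help of the forms, most secondary endpoints come from medical records, and the main inpatient resource items are endpoints in their own right. The early costs of a patient who dies can be read from the record, and the values after death are zero without any imputation. This objection stands and limits the point to items that need a reply.

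**Table 1 is not a contradiction.** A reader might see a conflict between the cost assessment marked at D30, D90 and D180 and cost forms given only at 3 and 6 months. The footnote groups the items as "Other secondary outcomes: postoperative length of stay, the intensive care unit (ICU) length of stay, re-admissions, cost assessment", in a row separate from the quality-of-life questionnaires. That fits costing from records at D30 with forms added later, and one row covering several outcomes need not mean that each is collected at every visit. A clarifying note would help, but no error is shown.

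**Economic methods may sit elsewhere.** Perspective, unit costs and utility calculation commonly belong to a full protocol or economic plan that is not shown, and their absence is no fault here. That also stands. It does not answer the point about {20c}, which is a stated rule. A later plan that imputed costs or utilities would contradict it.

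**Mitigation.** Under {18b}, local researchers contact patients about completing questionnaires. This should raise response, but it does not say what happens to the forms that are still missing. A patient without a 3-month form may also return the 6-month one, so non-response need not be total.

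**Conclusion.** The point holds in limited form. Section {20c} bars imputation of every missing outcome without exception, and out-of-hospital costs, productivity costs and EQ-5D-5L utilities depend on reply. As written, that part of the cost-effectiveness analysis is limited to responders and may be biased, because non-response is plausibly related to the complications that SDD targets.

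The size is not known. The 8% to 35% range rests on assumed response rates, on pneumonia as the sole cost driver and on equal response patterns in both arms. It applies only to the questionnaire-based share and does not model deaths. A single figure for the understatement, or a flat claim of bias towards zero, would go beyond the documents. The primary outcome is not affected. This is an inexpensive improvement to a secondary analysis.

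**What to change.** 1. In section {20c}, exempt questionnaire-based cost and utility items from the no-imputation rule. Multiply impute them using arm, the stratification variables, pneumonia, length of stay, ICU days and earlier EQ-5D-5L values, with a complete-case sensitivity analysis.
2. In Questionnaires and diaries, state that hospital resource use (index stay, ICU days, reoperations, readmissions to 6 months) is costed from medical records for all randomised patients, including those who die, and that costs and utility are zero after death. This is a clarification that the current text already allows.
3. As a further clarification, note in Table 1 which cost source the D30 mark refers to.

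The cost is protocol and analysis-plan wording plus some extra analysis work. The predictors are already collected, so no new visits are needed. The downside is reliance on a missing-at-random assumption, which the data cannot confirm. The complete-case analysis shows how far the result depends on the imputation.
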